### **Primary study endpoint analysis**

The primary endpoint is the reduction of renal urea clearance after 12 months of treatment compared between the two treatment groups.

The ITT population will be the primary analysis dataset, although an analysis on the PP population will also be performed.

### **Secondary endpoint analysis**

The following secondary efficacy endpoints will be analyzed using both the ITT and PP datasets.

Change in renal urea clearance and urine volume from randomization to each study visit will be summarized by randomized treatment arms. Serious adverse events will be summarized and listed by randomized treatment arm. Descriptive statistics will be calculated for each arm. All safety endpoints will be measured at each study visit, and use a per protocol population. Serum albumin, muscle mass, nutritional status, will be summarized and compared between treatment arms. SF-36 results will be summarized in each domain and in physical and mental component scores by treatment arm, and compared by randomized treatment arm at randomization. Raw scores from questions in each quality of life domain will be transformed to a 0 to 100 scale according to the following formula: Transformed score =  $[(\text{actual raw score} - \text{lowest possible raw score}) / (\text{highest possible raw score} - \text{lowest possible raw score})] \times 100$ .

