#### Adverse events, serious adverse events,

Adverse events leading to premature discontinuation and all events resulting in death will be assessed throughout the study.

**Investigation period:** 12 months 2 weeks (run-in: 2 weeks + evaluation 12 months)

**Data collection:** 5 points (Baseline at randomization, 3, 6, 9, and 12 months after randomization)

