#### **Analysis plan:**

For continuous variables, the descriptive statistics will be presented by number [N], mean and standard deviation [mean  $\pm$  SD] for normally distributed data, and minimum, median, interquartile ranges [Q1, Q3], and maximum for non-normally distributed data. For categorical variables, the number [N] and percentage [%] of each category will be calculated for non-missing data. Missing values will also be counted and reported in each variable for both continuous and categorical variables, if applicable. All analyses will be done per treatment and per time-point."

Treatment estimates and 95% confidence intervals will be calculated and used to assess primary and secondary efficacy endpoints between randomized treatment groups.

Continuous endpoints will be analyzed using ANCOVA or non-parametric equivalents. Longitudinal analyses for continuous endpoints will be conducted using general linear mixed model (GLM). Post-hoc pairwise comparisons will be conducted using Tukey's HSD. Binary endpoints will be analyzed using chi-square tests or logistic regression. The statistical test will be two-sided with significance level  $\alpha = 5\%$ . Due to the exploratory nature of the pilot study, P values will be interpreted as a merely descriptive-exploratory purpose."

For all endpoints and analysis populations, the primary treatment comparisons will be simple, unadjusted, two group comparisons. If there are important imbalances in baseline characteristics, then adjusted analyses will also be performed and presented in addition to unadjusted analyses.

Data on demographics, protocol and treatment compliance, concomitant medication and safety of all included subjects (including dropouts) will be included in the trial report. Demographics, safety data at randomization and concomitant medication will be listed. Descriptive statistics will be calculated for the subject characteristics. There will be no formal comparisons of randomized treatments for demographic and baseline characteristics (i.e. no p-values), as any imbalance will by definition have occurred by chance.

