### **The intention to treat (ITT) population**

The ITT population is defined as all participants who are randomized. Participants will be compared as randomized regardless of the treatment received. The following describes a framework for the analysis of the primary endpoint based on a particular handling of anticipated events:

In the event the patient dies the patient will be considered to have missing urea clearance and urine volume after that time point. In the event the patient become lost to follow up the latest available parameters will be used for the later time points. If the data at any time points are missing, the latest available parameters before that time points will be used instead.

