### **Per protocol (PP) population**

The PP population is defined as all participants included in the ITT population excluding those who deviate from the randomly assigned protocol for any reason. Analyses will be based on available data

and according to the treatment received, and patients will be censored once they cease their randomized treatment.

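### All safety endpoints are assigned to the per-protocol set, which is selected on behaviour that harm can drive and conflicts with the protocol's own commitments on safety reporting

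*Protocol*

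**What the plan says.** The Secondary endpoint analysis section of the protocol names one population for safety: "All safety endpoints will be measured at each study visit, and use a per protocol population". The rule at the head of that section, which calls for both ITT and PP analyses, is worded for efficacy endpoints, so it does not bring ITT to safety. No other safety set is named in the protocol.

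The section on the PP population defines the set by three operations on the ITT population:

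- exclusion: "excluding those who deviate from the randomly assigned protocol for any reason"
- grouping: "according to the treatment received"
- follow-up: "patients will be censored once they cease their randomized treatment"

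Three other statements bear on the same data:

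- Analysis plan: "safety of all included subjects (including dropouts) will be included in the trial report"
- Adverse events, serious adverse events: "Adverse events leading to premature discontinuation and all events resulting in death will be assessed throughout the study"
- Secondary endpoint analysis, shortly before the PP sentence: "Serious adverse events will be summarized and listed by randomized treatment arm"

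**The concern.** Membership of the PP set, and time at risk within it, depend on what happens after randomization, and harm is one of the things that can happen. A patient who gives up the low-protein diet or the ketoanalogues, or leaves the programme, because of an adverse event is one whom a safety table most needs to show. The plan removes that patient or stops counting at that moment.

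Group 2 starts with one dialysis session a week and less protein on non-dialysis days, so a reader will look closely at its harms. If harm-related stopping is more frequent in one arm, the PP comparison favours that arm. With 25 patients per arm, a few lost events can change the safety conclusion.

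**Working it through.** **Step 1. Set the statements side by side.**

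| Question | PP set, as assigned to safety | Statement elsewhere in the protocol |
|---|---|---|
| Who is counted? | Randomized patients minus all deviators | All included subjects, with dropouts (Analysis plan) |
| For how long? | Until randomized treatment stops | Throughout the study, for discontinuation events and deaths (Adverse events) |
| In which group? | Treatment received | Randomized arm, for SAEs (Secondary endpoint analysis) |

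The statements disagree on all three questions. The ITT definition ("The ITT population is defined as all participants who are randomized") would answer the first and third, but it is not applied to safety.

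**Step 2. Two readings of the PP definition.** The definition both excludes deviators and censors patients who stop; a patient must be in the set to be censored. The protocol does not say which clause governs a patient who stops treatment.

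- Exclusion reading: the patient and all of their events disappear. Adverse events leading to discontinuation would then be close to absent from the table.
- Censoring reading: the event that led to stopping is kept. Everything afterwards is lost, including a later death.

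**Step 3. The plan's own figures.** Sample Size Calculation gives 20 per arm, 20% drop-out and 25 per arm. Check: 20 / (1 − 0.20) = 25 per arm, 50 in total. This reproduces. The 20% is a drop-out rate. The PP set excludes by deviation, so its loss could be smaller or larger.

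**Step 4. Illustration under the exclusion reading.** The event counts are assumed; the documents give none. Let 8 of 25 patients in an arm have an SAE.

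- All randomized: 8/25 = 32%.
- Four of the eight excluded: (8 − 4)/(25 − 4) = 4/21 = 19.0%.
- Six of the eight excluded: (8 − 6)/(25 − 6) = 2/19 = 10.5%.

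If both arms truly have 8/25 but only one loses four such patients, the table shows 19.0% against 32%, a gap of about 13 percentage points created by the choice of set. If both arms lose four, each shows 19.0%: no spurious gap, but harm is understated in both.

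Under the censoring reading, if each of the eight had the SAE before or at the point of stopping, the count stays at 8/25 and only later events are missing.

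**Step 5. Sensitivity to how far leaving is related to harm (exclusion reading, assumed risks).** Let 5 of 25 leave (20%), with event risk 10% in the 20 who stay and q in the 5 who leave. Risk in all randomized = (5q + 20 × 0.10)/25. The PP set shows 10% whatever q is.

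| q | All randomized | PP | Expected events lost (5q) |
|---|---|---|---|
| 10% | 10% | 10% | 0.5 |
| 40% | 16% | 10% | 2 |
| 80% | 24% | 10% | 4 |
| 100% | 28% | 10% | 5 |

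With q = 80%, the risk in all randomized patients runs from 15.6% with 2 leavers to 32.4% with 8, against 10% in PP.

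**Step 6. Loss even when leaving is unrelated to harm.** The chance of seeing at least one case of an event with 5% risk is 1 − 0.95^n: 72% at n = 25 and 64% at n = 20.

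**The case against.** **Escalation of dialysis.** A reader might infer that a patient moved off once-weekly dialysis for water retention, hyperkalemia or malnutrition drops out of the safety analysis. The protocol does not support that. These are listed among the criteria for remaining on once-weekly dialysis, and failing them leads to a higher frequency. Group 2 is defined as an incremental programme, so moving up is on its face part of the assigned strategy and need not be a deviation. (The group labels in the paragraph on raising frequency do not match the criteria headings and must be reconciled, but the incremental scheme is clear.) The concern bears mainly on stopping the diet or ketoanalogues, and on withdrawal.

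**Size.** It is also tempting to say that discontinuation events would be about 0% whatever the true rate, or that up to 10 of 50 patients leave the safety set. The first holds only under the exclusion reading. The second treats planned drop-out as the deviation rate; it is neither an upper bound nor a deviation rate, and under censoring dropouts still contribute until they leave.

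**Softness of the conflict.** The Analysis plan could mean full listings for everyone alongside a PP comparison, and the Safety Reporting section requires all SAEs to be reported. So SAEs in patients who stop would not go unreported. But the protocol does not draw a line between listing and analysis, and the PP sentence covers every safety endpoint.

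**Direction and purpose.** PP exclusion applies to both arms, so bias in favour of Group 2 requires more harm-related stopping there, which no figure in the protocol shows. The trial is an exploratory pilot, its objectives include no safety comparison, and its primary ITT analysis is unaffected. These points limit the consequence. They do not make PP a sound sole set for safety.

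**Conclusion.** The point stands. It rests on a positive statement in the protocol, not on detail that a separate SAP might supply. As written, safety is analysed only in a set chosen by post-randomization behaviour, and that choice conflicts with three other statements in the same document. Under either reading of the PP definition some safety events can be lost; the readings differ in how many.

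The size cannot be fixed from the protocol. The drop from 32% to 19% assumes eight patients with an SAE, four of them excluded, and the exclusion reading. The 24% against 10% assumes five leavers at 80% risk and stayers at 10%. Understatement requires that leaving be related to harm or that events occur after stopping. A distorted comparison further requires that this differ between arms. It should be corrected before analysis, because the safety results otherwise depend on an unsettled and selective definition.

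**What to change.** In Secondary endpoint analysis, replace the clause that assigns safety to the PP set with wording such as: all safety endpoints will be analysed in all randomized patients (or all who received any randomized treatment), by randomized arm, counting every event from randomization to month 12 regardless of deviation, escalation of dialysis frequency or discontinuation; any per-protocol safety table is supplementary.

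Then align the related text. The Analysis plan and the Adverse events section should refer to this population. The PP section should say whether a patient who stops treatment is excluded or censored, and whether escalation under the protocol's criteria counts as a deviation.

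The cost is a few sentences. Adverse event collection is already required. The one operational check is that events continue to be collected to month 12 in patients who stop randomized treatment. No change to sample size or to the primary analysis is needed.

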### **The intention to treat (ITT) population**

The ITT population is defined as all participants who are randomized. Participants will be compared as randomized regardless of the treatment received. The following describes a framework for the analysis of the primary endpoint based on a particular handling of anticipated events:

In the event the patient dies the patient will be considered to have missing urea clearance and urine volume after that time point. In the event the patient become lost to follow up the latest available parameters will be used for the later time points. If the data at any time points are missing, the latest available parameters before that time points will be used instead.

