**Methods:**

**Sample Size Calculation:**

As this is a pilot study, the sample size calculation will be based on recent suggestions for sample size estimation in pilot randomized trials by Whitehead et al. With 80% power and the alpha level = 5%, 20 patients per treatment arm are required based on the non-central t distribution (NCT) approach assuming a small standardized effect size ( $0.1 \leq \delta < 0.3$ ). With an anticipated the drop-out rate of 20%, 25 patients per treatment arm are adequate. Therefore, we aim to include a total of 50 patients in the study.

Target number of Patients: 50 incident hemodialysis patients will be randomized 1: 1 according to the frequency of dialysis per week, amount of protein prescribed, and receiving of ketoanalogues. Additionally, the different techniques of hemodialysis will be stratified by dialysis facilities as the followings (Fig 1):

- **Group 1:** Twice weekly HD program plus regular protein diet (1.0 g/kg/day) every day
- **Group 2:** Incremental HD program, starting from once weekly HD/HDF plus low protein diet (0.6 g/kg/day) and ketoanalogues supplementation on non-dialysis days and regular protein diet (1.0-1.2 g/kg/day) on dialysis day

[figure not shown]

(Figure S1)

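### Carrying the last urea clearance forward in the primary ITT analysis hides part of each drop-out's decline, so the 12-month comparison is biased when loss differs between arms and a true effect is diluted when it does not

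*Protocol*

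**What the plan says.** The endpoint, under Primary study endpoint analysis, is a 12-month change: "The primary endpoint is the reduction of renal urea clearance after 12 months of treatment compared between the two treatment groups". The same section sets the dataset: "The ITT population will be the primary analysis dataset, although an analysis on the PP population will also be performed".

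The section on the ITT population then fixes the handling of missing data and ties it to that endpoint: "The following describes a framework for the analysis of the primary endpoint based on a particular handling of anticipated events". It gives three rules:

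- Death: "In the event the patient dies the patient will be considered to have missing urea clearance and urine volume after that time point".
- Loss to follow-up: "In the event the patient become lost to follow up the latest available parameters will be used for the later time points".
- Anything else: "If the data at any time points are missing, the latest available parameters before that time points will be used instead".

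The second and third rules are LOCF. Visits are at baseline and 3, 6, 9 and 12 months.

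The Analysis plan makes the primary comparison a plain, unadjusted comparison of the two arms. It also names a mixed model, but for longitudinal analyses. Sample Size Calculation allows for 20% drop-out.

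**The concern.** LOCF assumes that nothing changes after the last visit. The protocol's own Rationale describes residual kidney function as declining once dialysis starts, at a rate that depends on the dialysis schedule. Carrying a value forward therefore credits each drop-out with function that the trial did not observe. Preserved function is also the result that the trial hopes to show.

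Two things are at stake. If the arms lose patients at different rates or at different times, the arm with more or earlier loss looks better for that reason alone. If they lose patients alike, a real difference is diluted. The carried-forward values also enter the two-group comparison as if they had been measured, so the confidence interval does not reflect that they are guesses.

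Unequal loss is not far-fetched. The arms differ visibly in dialysis frequency, protein prescription and tablets. The protocol does not predict an imbalance, however.

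**Working it through.** **The plan's own figure.** 20 evaluable per arm ÷ (1 − 0.20) = 25 per arm, as stated. At 20% drop-out, 0.20 × 25 = 5 patients per arm could have a carried-forward 12-month value.

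**Inputs from the protocol.** Visits at 0, 3, 6, 9 and 12 months; 25 per arm; 20% drop-out; two-sided 5% test; unadjusted two-group comparison.

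**Assumed inputs (not in the protocol).** Linear decline of b mL/min/month, and last visit equally likely at month 0, 3, 6 or 9. The months of decline lost per drop-out then average (12 + 9 + 6 + 3)/4 = 7.5.

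**Formula.** With drop-out proportion p, the mean reduction under LOCF is b × (12 − 7.5p) instead of 12b. The bias in favour of arm A over arm B is 7.5 × (b_A p_A − b_B p_B).

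**No true effect, 30% versus 10% drop-out.**

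| Decline per month | Bias = 7.5 × b × (0.30 − 0.10) |
|---|---|
| 0.15 | 0.225 mL/min |
| 0.25 | 0.375 mL/min |

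The bias favours the arm that loses more patients.

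Simulation with 25 per arm, baseline 5 (SD 1.2), slope SD 0.1, measurement SD 0.5 and clearance floored at zero gives 0.21 to 0.22 and 0.35 to 0.36 mL/min. The floor explains why the larger figure falls slightly below 0.375. Rejection rates are about 9% and 14%, against a nominal 5%.

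**No true effect, 20% in both arms, same timing.** Bias = 7.5 × b × (0.20 − 0.20) = 0, and simulated rejection is 5%.

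**True effect, 20% in both arms.** Each arm's mean reduction, and so the difference, is multiplied by 1 − 7.5 × 0.20/12 = 0.875, which is 12.5% attenuation. For declines of 0.2 and 0.1 per month the true difference is 12 × 0.1 = 1.20 mL/min, and LOCF gives 1.05.

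**True effect, unequal drop-out (0.2 standard, 0.1 incremental).**

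- 10% standard, 30% incremental: 0.2 × (12 − 0.75) − 0.1 × (12 − 2.25) = 2.25 − 0.975 = 1.275, an overestimate.
- 30% standard, 10% incremental: 0.2 × (12 − 2.25) − 0.1 × (12 − 0.75) = 1.95 − 1.125 = 0.825, an underestimate.

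**Same rate, different timing.** Take 0.2 per month, 20% drop-out and no true effect. If one arm's drop-outs are last seen at month 9 and the other's at baseline, the bias is 0.2 × 0.20 × (12 − 3) = 0.36 mL/min.

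**Is there a check elsewhere?** The per-protocol analysis uses available data but removes everyone who deviates from the assigned protocol. It changes the population as well as the handling of missing values, so it cannot show what LOCF does within the ITT set.

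**The case against.** **This is a pilot, and the imbalance is hypothetical.** The protocol calls P values descriptive and exploratory and gives a single 20% drop-out figure. With no true effect and alike loss there is no bias, and with a true effect alike loss is conservative. All of this stands, and it lowers the severity. It does not remove the point, because the plan reports treatment estimates with 95% confidence intervals under a superiority objective, and both are affected.

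**Stronger readings that a reader might infer, and why they do not hold:**

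- *LOCF causes a large loss of power.* At 20% drop-out in both arms and a difference of about 1.1 to 1.2 mL/min, power falls from about 84% on complete data to about 66% to 78% under LOCF. Completers alone give about 73% to 76%, so most of the fall is drop-out itself.
- *The bias favours the incremental arm.* The direction depends on which arm loses more patients, or loses them earlier. The protocol does not say.
- *Deaths are scored as preserved function.* The specific rule on death leaves later values missing and most naturally governs. The later sentence on missing data makes no exception for death, so a clarifying clause is worth adding, but no more than that.
- *Patients who stop passing urine keep their last positive clearance.* The protocol does not say that absent urine is coded as missing. Zero urine volume can be read as an observed clearance of zero.
- *Carried-forward values feed the mixed model.* The LOCF rules are framed for the primary endpoint, and nothing says that they apply to the longitudinal model.

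**Conclusion.** The point holds and should be fixed. The protocol itself fixes LOCF as the primary rule for an endpoint that it describes as declining, so this is not a detail left for an analysis plan to settle. That a patient lost before month 3 scores zero reduction follows from the rule alone.

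The sizes are conditional. The false benefit of about 0.2 to 0.36 mL/min, with type I error of about 9% to 14%, needs 30% versus 10% drop-out, a decline of 0.15 to 0.25 mL/min/month and evenly spread last visits. The attenuation of about 12% needs only the planned 20% in both arms with the same timing pattern and linear decline. The simulated error rates also depend on assumed SDs. The documents do not support a claim that the trial will be biased in a known direction.

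**What to change.** 1. In the section on the ITT population, replace the two carry-forward sentences with a likelihood-based mixed model for repeated measures on all observed visits (0, 3, 6, 9 and 12 months). The primary estimate is the arm difference at month 12. Treating baseline as one of the modelled visits keeps patients who have only a baseline value in the ITT analysis.
2. In the Analysis plan, amend the sentence that makes the primary comparison unadjusted so that it names this model. Otherwise the two sections would contradict each other.
3. Keep LOCF, if wanted, only as a sensitivity analysis.
4. Add one clause saying that the general rule for missing values does not apply after death.
5. State that clearance is recorded as 0 when urine output has ceased.

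The cost is wording only: the mixed model is already named in the protocol, and no extra data are needed. The downsides are reliance on a missing-at-random assumption and a somewhat wider confidence interval than LOCF's artificially complete data would give.

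### Carrying the last clearance forward in the primary ITT analysis overstates preserved function in dropouts: it dilutes a true difference and, if dropout is unequal, biases the arm comparison

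*Protocol*

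**What the plan says.** Under Primary study endpoint analysis the Protocol states: "The primary endpoint is the reduction of renal urea clearance after 12 months of treatment compared between the two treatment groups". It continues: "The ITT population will be the primary analysis dataset, although an analysis on the PP population will also be performed".

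The section on the ITT population then sets rules for anticipated events, described as a framework for analysing the primary endpoint. There are three:

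- Death: "In the event the patient dies the patient will be considered to have missing urea clearance and urine volume after that time point".
- Loss to follow-up: "In the event the patient become lost to follow up the latest available parameters will be used for the later time points".
- Any other gap: "If the data at any time points are missing, the latest available parameters before that time points will be used instead".

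The last two are last-observation-carried-forward for living patients. No sensitivity analysis to this rule is stated.

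Elsewhere, the Analysis plan lists a mixed model for longitudinal analyses of continuous endpoints, but makes the primary comparison a plain two-group one without adjustment. It also says that P values serve only a descriptive, exploratory purpose. For the PP set, "Analyses will be based on available data". The sample size section expects 20% dropout, and visits are at baseline and months 3, 6, 9 and 12.

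**The concern.** Carry-forward gives the right month-12 value only if clearance stops changing once a patient leaves. The Protocol's Rationale says otherwise: it treats residual function as declining and justifies the trial by a difference in the rate of decline. The rule therefore errs in one direction. A patient lost before month 3 is scored as having no reduction at all. A patient last seen at month 9 still has three months of decline removed.

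Two consequences follow for the arm comparison. If the arms lose patients at the same rate and time, both declines are understated and a true difference is diluted. If they do not, a bias towards the arm with more or earlier loss is added to whatever the treatment does. Unequal loss is plausible because the arms differ openly in dialysis frequency, diet and tablets, although the Protocol gives no arm-specific rate. What is at stake is the primary estimate and its 95% confidence interval, which the Analysis plan uses to assess the endpoint.

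**Working it through.** **Inputs from the Protocol.** 20 per arm before dropout; 20% dropout; visits at 0, 3, 6, 9 and 12 months; two-sided 5%. The dropout inflation reproduces: 20 / (1 - 0.20) = 25 per arm, 50 in total.

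**Inputs that must be assumed.** The Protocol gives no within-arm decline, no SD and no dropout by arm. The figure of 0.58 ml/min/month in the Rationale is a difference between regimens, not a rate for either arm here. Assumed: 12-month declines of 1 to 3 ml/min, and a last visit equally likely at months 0, 3, 6 or 9.

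**Share of decline erased.** Mean last visit = (0 + 3 + 6 + 9) / 4 = 4.5 months, so each dropout loses 1 - 4.5/12 = 0.625 of the true decline. The extremes are 3/12 = 0.25 (all last seen at month 9) and 1.0 (all lost before month 3).

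**Formula.** With true decline D and dropout share p, the expected recorded reduction in an arm is D x (1 - 0.625p). The estimated difference is D1 x (1 - 0.625 p1) - D2 x (1 - 0.625 p2).

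**Equal dropout.** With p = 0.20 in both arms, each decline is multiplied by 1 - 0.125 = 0.875. A true difference of 1.2 ml/min (declines 2.4 and 1.2) becomes 2.10 - 1.05 = 1.05. Over the extremes above, the dilution runs from 0.20 x 0.25 = 5% to 0.20 x 1.0 = 20%. A simulation that also floors clearance at zero turned a true 1.0 into 0.85.

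**Unequal dropout, no true effect.** The false difference is D x 0.625 x (p2 - p1). Error rates are simulated two-sided rejection rates with 25 per arm, baseline 4.5 (SD 1.2) ml/min, slope SD 0.08 ml/min/month, measurement SD 0.6 ml/min and a floor at 0.

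| Decline (ml/min) | Dropout | False difference (ml/min) | Simulated error |
|---|---|---|---|
| any | equal | 0 | about 5% |
| 1.0 | 12% v 28% | 1.0 x 0.625 x 0.16 = 0.10 | 5.6% |
| 2 | 16% v 24% | 2 x 0.625 x 0.08 = 0.10 | 6.0% |
| 1.2 | 10% v 30% | 1.2 x 0.625 x 0.20 = 0.15 | 7.5% |
| 2 | 10% v 30% | 2 x 0.625 x 0.20 = 0.25 (simulated 0.24) | about 10% |
| 3 | 10% v 30% | 3 x 0.625 x 0.20 = 0.375 (simulated 0.34) | about 14% |

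The SD of the 12-month change implied by those assumptions, ignoring the floor, is sqrt((0.08 x 12)^2 + 2 x 0.6^2) = 1.28 ml/min. The range 0.10 to 0.375 is therefore about 0.08 to 0.29 SD. The sample size section works with effects of 0.1 to below 0.3 SD.

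**Unequal dropout with a true effect.** Declines 2.4 and 1.2, true difference 1.2:

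- Dropout 7 v 3 of 25, more in the faster-declining arm: 2.4 x 0.825 - 1.2 x 0.925 = 1.98 - 1.11 = 0.87.
- Dropout 3 v 7: 2.4 x 0.925 - 1.2 x 0.825 = 2.22 - 0.99 = 1.23.

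In a second simulation (slope SD 0.1 ml/min/month, measurement SD 0.4 ml/min), power under carry-forward was about 79% with 5 v 5 dropouts and 60% with 7 v 3. In the same runs, comparing only observed 12-month changes gave estimates of 1.19 to 1.21 and power of 78% to 80%. Dropout there was unrelated to outcome.

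**The case against.** The best defence is that this is a pilot of 50 patients whose P values are declared exploratory, so a raised type I error misleads no formal test. With equal dropout the bias works against a superiority claim. The large false differences need both a steep decline and a threefold dropout ratio. The 20% may also include deaths, which are not carried forward. All of this is fair, and it lowers the urgency. It does not remove the bias from the estimate and interval, and the primary objective is still worded as showing superiority.

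Some stronger readings are tempting, but the text does not support them:

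- *A patient who stops making urine becomes missing and keeps the last positive clearance.* The Protocol does not say how an empty timed collection is recorded; it could equally be zero.
- *The arm losing more patients looks better whatever the treatment does.* The bias is added to the true effect and does not replace it. In the 7 v 3 example above, the better-preserving arm still comes out ahead.
- *The planned mixed model will be fitted to filled-in data.* The mention of later time points allows this, but nothing states it.
- *ITT and PP must share one missing-data method.* A PP analysis on available data does give one analysis without carry-forward. It is not a clean check, because the population changes too, but uniform handling is largely a preference.

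The evidence for the remedy also has limits. One run of 339 trials with a random-slope model (decline 2, dropout 10% v 30%) gave a false difference of 0.05 on observed data against 0.29 on carried-forward data, with a Monte Carlo error of about 0.02. That is not exactly the visit-by-arm model recommended here. Any such model also relies on dropout being explained by the observed data.

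**Conclusion.** The concern holds: carry-forward is fixed in the primary ITT analysis of an endpoint the Protocol itself expects to fall, and it overstates preserved function, on average, in living patients with no month-12 value. The direction needs only a declining endpoint. The size rests on assumptions:

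- Equal dropout at 20% dilutes a true difference by about 12.5%, given evenly spread last visits.
- With no true effect, the false difference is zero under equal dropout. It is about 0.10-0.15 ml/min, with error of about 6% to 7.5%, in mild scenarios.
- It is 0.24-0.25 ml/min with about 10% error at decline 2, and 0.34-0.38 ml/min with about 14% error at decline 3, both with 10% v 30% dropout.

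Since P values are exploratory, the weight falls on the biased estimate and interval rather than on the error rates. This should be fixed, but it does not invalidate the trial. The point does not concern deaths, for which the Protocol has a separate rule.

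**What to change.** 1. In the ITT population section, delete carry-forward as the primary rule for loss to follow-up and missed visits.
2. Estimate the month-12 arm difference in the ITT set with the mixed model already named in the Analysis plan, fitted to all observed visits without fill-in, with terms for visit, arm, arm-by-visit and baseline clearance.
3. Amend the Analysis plan sentence that makes the primary comparison unadjusted, since it would contradict step 2. The same section already names ANCOVA for continuous endpoints.
4. Keep carry-forward at most as a labelled sensitivity analysis.
5. As a clarification only, state that a timed collection yielding no urine is scored as zero clearance, not as missing.

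The cost is wording in two sections. The visits and the model are already planned and no new data are needed. The confidence interval may be slightly wider, because filled-in values no longer count as data.
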